**Figure 2 fig2:**
[figure not shown]
Basic design of a MOVI-ageing session. MVPA, Moderate-vigorous physical activity; MPA, moderate physical activity; CD, cognitive demands.

To ensure the standardization of the program, at the beginning of the intervention, participants in the IG will attend a 2-h training session for the use of the platform and will be instructed in the control of their heart rate during the execution of the physical exercise program to be able to control the intensity of the physical exercise they perform. Users will be provided with indications to carry out the activities and will be required to perform at least 3 sessions per week of cognitively demanding physical exercise through the platform for 12 weeks.

#### Criteria for nonadherence and prolongation of training

Compliance with the exercise program will be regularly monitored through the intervention. To be considered in the analyses, participants must attend at least 70% of the sessions. If, due to unexpected circumstances, a participant does not comply with the exercise program within the 12 weeks, the training program may be extended for up to 4 weeks. Finally, in case of unexpected adverse effects of the intervention, the participant will be clinically followed-up, and the research team will record the reasons for drop out.

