### Recruitment and allocation

The Clinical Research Ethics Committee of the ‘Virgen de la Luz’ Hospital in Cuenca has approved the study protocol (registration number: 2022/PI3222). The development of this project will be supported by the Health Care Services of Cuenca. In addition, this protocol has been previously registered in Clinicaltrials.gov (Number: NCT05928078).

Potential participants will be accessed through key informants in the social centers of Cuenca and Talavera de la Reina. The research team will contact the potential participants by phone to offer them participation in the study. In addition, flyers and posters will be located in places where older people could potentially develop leisure activities (including but not limited to libraries and older adults’ centers) with the contact information of the research team.

During the information process of the participants, the research team will inform them that they can drop out of the study as they request. After agreement to participate and informed consent, participants will be randomly distributed (1:1) to the intervention (IG) or control group (CG) using EPIDAT 4.2 software (Figure 1).

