### MOVI-ageing intervention: description

The MOVI-ageing intervention will be developed as a randomized controlled trial with two arms in which participants will be randomly assigned to the IG, in which a home-based e-Health intervention of cognitively demanding exercise will be performed, or to the CG in which participants will continue their regular daily activity.

The e-Health intervention will be delivered using a platform including videos that will guide the participants in the realization of the movement during the cognitively demanding physical exercises. The participants will follow the videos remotely and off-line, and the users will have to imitate the movements of the trainer. Through the platform, it will be possible to evaluate the degree of compliance with the exercise program and the correct performance, as the system will accurately track and measure the participant’s limb movement through the camera and provide the research team with an objective measure of the patient’s movements and progress. Research team will be able to check this information during the development of the session or at any time of the clinical trial duration.

The recorded videos, designed by a team of experts including nurses, psychologists, physical activity graduates, and geriatricians, will include cognitively demanding exercises involving both basic cognitive functions (i.e., inhibition, working memory, and cognitive flexibility) and higher cognitive functions (i.e., spatial orientation, numerical calculation, and semantics). Each video will include a standardized physical exercise program structured as follows: 5 min warm-up (including animation and/or joint mobility activities), three blocks of 4 min at 65–75% of the maximum heart rate (including aerobic and muscle strength activities) without cognitive demand, three blocks of 4 min at moderate intensity including cognitively demanding activities, and 10 min of cool-down (including balance activities, breathing-relaxation exercises, and/or muscle stretching) (Figure 2).

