### Statistical analysis

#### Sample size

Previous studies (30) have shown that a combined program of exercise and cognitive training for 3 months can improve working memory in cognitively healthy older adults, with an approximate effect size of 0.9. Considering the characteristics of our study and using GPower software, we calculated that a sample size of 21 participants per group would be needed to achieve a power of 0.8, with an alpha of 0.05 and a beta of 0.2. Assuming a dropout rate of 15%, a final sample size of 24 participants per group would be required for the efficacy and feasibility study. The sample size for the implementation study will be calculated based on the results of the previous phase.

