#### Analyses of outcomes

After measurements, participants’ data will be entered into a database by two independent researchers. Blinding on handling data will be assured by separating measurement values from general participant information.

The statistical analysis plan can be summarized as follows: (i) after checking that randomization has been effective, we will winsorize the variables to limit the influence of extreme values; this will be done by replacing values below the 1st percentile with the 1st percentile value and those above the 99th percentile with the 99th percentile value. (ii) Mixed regression models will be used in which each outcome variable will be the dependent variable, interventions will be treated as fixed effects (1 = IG and 0 = CG), and the models will be adjusted for baseline reference values and age. The results will be expressed as absolute differences in changes in the variables between baseline and final measurement. When the dependent variable is dichotomous, odds ratios (ORs) will be calculated. Finally, (iii) analyses will be conducted from an intention-to-treat perspective, whereby participants will remain in the group to which they were originally assigned, regardless of the degree of compliance with the intervention.

The results will be considered statistically significant when *p* < 0.05. The analyses will be performed using STATA16.

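### The protocol makes at least 70% attendance a condition for being analysed and also promises intention-to-treat regardless of compliance; both cannot be applied, and the attendance rule can remove only intervention participants

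*Protocol article*

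**What the plan says.** Two sections of the protocol article decide who enters the analyses.

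- *Criteria for nonadherence and prolongation of training*: "To be considered in the analyses, participants must attend at least 70% of the sessions". The sentence is not limited to a per-protocol or sensitivity analysis. The same paragraph adds that, if a participant has not complied within the 12 weeks because of unexpected circumstances, "the training program may be extended for up to 4 weeks". It does not say what happens to someone still below 70% after that.
- *Analyses of outcomes*: "analyses will be conducted from an intention-to-treat perspective", and "participants will remain in the group to which they were originally assigned, regardless of the degree of compliance with the intervention".

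Neither section refers to the other, and the article defines no separate per-protocol set.

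The intervention description shows to whom an attendance rule can apply. Intervention participants must "perform at least 3 sessions per week of cognitively demanding physical exercise through the platform for 12 weeks". The comparator is "the CG in which participants will continue their regular daily activity", which involves no sessions.

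**The concern.** Both statements speak of analyses in general, so the conflict covers the primary cognitive endpoints and every other outcome. Whoever writes the detailed analysis plan could follow either sentence and claim to follow the protocol. Participants are not blinded and the platform records compliance, so the choice could be made once attendance is known.

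The two rules also differ in validity. Keeping everyone as assigned preserves the randomised comparison. The attendance rule conditions on behaviour that arises after randomisation and in one arm only. People who keep up a cognitively demanding programme may differ in prognosis from those who do not, and the control group is not filtered in the same way. A distorted estimate would also carry forward, because the *Sample size* section bases the size of the implementation study on the results of this phase.

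**Working it through.** **1. The two rules applied to one participant.** Take an intervention participant with 60% attendance and a final measurement.

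| Rule | Result |
|---|---|
| Nonadherence section (at least 70% to be analysed) | excluded |
| Analyses section (as assigned, whatever the compliance) | included |

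No reading of the two sentences gives the same answer for this participant.

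**2. The threshold.** Minimum sessions: 3 per week × 12 weeks = 36. Then 0.70 × 36 = 25.2, so at least 26 sessions. Controls have none, so the rule can exclude only from the intervention arm.

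**3. The plan's own figure.** A two-sided two-sample t test with standardised effect 0.9, alpha 0.05 and power 0.80 gives n = 20.39, so 21 per group (power at 21 = 0.812), as stated. Resolving the contradiction as intention-to-treat changes no stated figure. The planned 24 per group is used below only to set the scale.

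**4. Illustration of the bias.** Assumptions, none of them from the documents:
- no true effect, and 24 randomised per arm;
- a latent standard normal attendance tendency in the intervention arm, with a share f of participants above the threshold;
- correlation r between that tendency and the outcome, for prognostic reasons. Because the models adjust for baseline value and age, r is what remains after that adjustment, and the SD is that of the adjusted outcome.

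With c = Φ⁻¹(1 − f), the spurious difference is r × φ(c) / f.

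- f = 0.8: φ(−0.842)/0.8 = 0.280/0.8 = 0.350
- f = 0.7: φ(−0.524)/0.7 = 0.348/0.7 = 0.497
- f = 0.6: φ(−0.253)/0.6 = 0.386/0.6 = 0.644

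Multiplying by r, with the type I error of a nominal 5% two-sided t test found by simulation:

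| f | r = 0.1 | r = 0.3 | r = 0.5 |
|---|---|---|---|
| 0.8 | 0.035 SD, about 5.2% | 0.105 SD, about 6.3% | 0.175 SD, about 8.6% |
| 0.7 | 0.050 SD, about 5.2% | 0.149 SD, about 7% | 0.248 SD, about 12% |
| 0.6 | 0.064 SD, about 5.4% | 0.193 SD, about 9% | 0.322 SD, about 16% |

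The range runs from negligible to material. The documents do not say where in it the trial would lie.

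**The case against.** The best defence is that the statistical section governs and already commits to intention-to-treat, so the attendance sentence is a loosely worded per-protocol definition. That may be what was meant, but the sentence says nothing of the kind and no per-protocol set exists for it to define. Nor can intention-to-treat be read as only forbidding a change of group: the text says compliance does not matter, and dropping people for low compliance contradicts that.

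Other objections limit the size of the problem and stand to that extent. The possible 4-week extension, weekly feedback and monthly contact should reduce the number below 70%. Adjustment for baseline value and age should absorb part of any selection of fitter or cognitively better participants. Neither removes the conflict, nor any selection through motivation, intercurrent illness or a declining course.

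Three stronger readings are tempting but unsupported:

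- **A reader might infer that the attendance rule costs power.** With 20.4 per arm (24 × 0.85), power at 0.9 is 0.80. If 30% of the intervention arm is then excluded, 14.3 against 20.4 gives 0.72. That holds the effect at 0.9 in both cases. Under intention-to-treat, the 30% would plausibly dilute it: if they gain nothing, 0.7 × 0.9 = 0.63 and power is about 0.50; if they gain half, 0.85 × 0.9 = 0.765 and power is about 0.66. Both are below 0.72. The reason to prefer intention-to-treat is validity, not power.
- **A reader might infer that the 15% dropout allowance fails to cover these exclusions.** The article does not define dropout, so it may include people lost through non-adherence.
- **A reader might infer that the bias certainly favours the intervention.** That direction is probable; the documents do not establish it.

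**Conclusion.** The contradiction is real and lies in the article's own text; it is not a detail left to an analysis plan. It needs no calculation: one rule excludes the participants that the other retains, for every outcome. If followed, the attendance rule would replace a randomised comparison with a selected subset of the intervention group against all controls, probably favouring the intervention.

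The size of the bias cannot be derived from the documents. Under the stated assumptions (60–80% adherent, residual correlation 0.1–0.5, no true effect, 24 per arm) it is roughly 0.03–0.32 SD, with type I error roughly 5–16%. These figures are illustrative, and the lower end is close to harmless. The point should nevertheless be settled before the analysis, because the main efficacy result cannot be interpreted until it is clear who is in it.

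**What to change.** - In *Criteria for nonadherence and prolongation of training*, delete the sentence as a condition for being analysed.
- In *Analyses of outcomes*, state that the main analysis of every outcome includes all randomised participants in their assigned group, whatever their attendance. The *Variables* section already plans end-of-phase measurements on all participants, so no new data collection is needed; those measurements should be used for low attenders too.
- Keep attendance of at least 70% only as the definition of a secondary per-protocol analysis, labelled as a non-randomised comparison.

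The cost in text is one sentence removed and one or two added. The real downside is that the estimated effect may be smaller, because participants who attend little dilute it, and the dilution may not be trivial. In the illustration above with 30% non-attenders, an effect of 0.9 becomes 0.63 to 0.765, which is 15–30% smaller.

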#### MOVI-ageing: monitoring and adherence

To improve adherence to the intervention, a telephone number and an email address will be available for participants for any doubt or information they need. Weekly information on the amount of physical activity performed will be emailed to the participants. The research team will contact participants monthly to check their satisfaction with the intervention.

### Variables

Measurement of the variables will be performed on all participants at the beginning and at the end of each phase of the study. Each participant will be scheduled at the facilities of the research team to carry out the measurements of all variables on a single day, and investigators will be previously trained to standardize the measurements. The variables will be measured following standardized and validated processes with the following tools (Table 1):

Basic executive functions: using the NIHtool (16) and including (a) Attention using the Eriksen flanker Task test where a 40-trial block will be presented consisting of a pseudorandom sequence of congruent and incongruent trials. Scoring will be calculated based on accuracy and reaction time; (b) Working memory using an adaptation of the Mungas List Sorting task where a series of illustrated pictures will be presented visually and orally. Participants will be asked to verbally repeat the names of the pictures in order of size, from smallest to largest. Two list versions will be presented, the first presenting items in one category (i.e., animals), and the second presenting items in 2 categories (i.e., animals and food) in which participants will be asked to organize items by category and size; and (c) cognitive flexibility using the DCCS (Dimension Change Card Sort) test. This tool will present a 30-trial block of mixed by “color” or “shape” stimulus, where participants will be asked to adapt their response according to the relevant dimension.Global cognitive function with the Mini-Mental State Examination (MMSE) (17), which consists of 30 items grouped into 11 categories (including visual space, memory, naming, attention, calculation, abstract, orientation, and language function), with higher scores representing better cognitive functioning. The MMSE has been widely used in older people and has excellent reliability and validity (18). In this study, cognitive impairment will be defined as an MMSE score of less than 24 for respondents with 8 years of education or more and less than 20 for those with less than 8 years of education (19).Health-related quality of life (HRQoL) with the SF-12 test (20), which aimed to evaluate the intensity and/or frequency of people’s state of health. The scale is composed of 12 items that could be answered by a Likert-type scale. This questionnaire provides information on eight subscales: physical functioning, physical role, bodily pain, general health, vitality, social functioning, emotional role, and mental health. These eight subscales comprise the physical and mental domains of patients’ HRQoL, where the higher the score is, the better the HRQoL. The SF-12 is a valid and reliable instrument.Depression, anxiety, and stress will be assessed with Yesavage’s 15-item Geriatric Depression Scale (GDS) questionnaire (21, 22), which includes questions related to affect, in-activity, irritability, isolation, distressing thoughts, or negative judgments. The questions have dichotomous answers (yes/no) regarding the last week.Cardiorespiratory fitness measured with the 6-min walking test (6MWT), where participants will be instructed to “walk as far as possible” for 6 min back and forth along a corridor 100 feet in length (23). Participants will be encouraged to walk but permitted to slow down, stop, and rest when needed. This test reflects the overall functional ability and the impact of multiple factors on exercise capacity (24).Muscular strength will be measured by upper extremity dynamometry with the digital TKK 5401 Grip-D (Takey^®^, Tokyo, Japan). This test measures the upper body strength in kilograms. The test will be performed twice with the right hand and twice with the left hand; the mean average of the 4 measurements will be calculated.Physical activity will be measured with the Axivity 6-axes accelerometers (Axivity LTd.) for seven consecutive days (including nights), with a fixed frequency of 30.0 Hz to collect raw acceleration data measured in “g” for each movement axis (x, y, and z). Data will be expressed in units of milligrams (1,000 mg = 1 g = 9.81 m/s^2^). We will consider as valid registers of ≥5 days, including 1 weekend day.Physical function will be measured with the Short Portable Physical Battery scale (SPPB), (25) which measures balance, walking speed, and standing up and sitting on a chair 5 times. During the balance test, the participants will be required to maintain 3 positions for 10 s each: feet together, semitandem, and tandem. In the walking speed test, the participant will be encouraged to walk a 4 m distance at his/her usual pace. This test will be performed 2 times, and the shortest time will be recorded. Finally, the total time the participant spent standing up and sitting 5 times on a chair will be recorded. Each test could be scored from 0 (worst performance) to 4 (best performance). In addition, the score for the total battery will be the sum of the 3 tests and ranges from 0 to 12.The concern of falling with the Falls Efficacy Scale International (FES-I) (26), which includes the possibility of falling when performing 16 different everyday life activities. Each item could be classified as follows: 1 = not at all concerned, 2 = somewhat concerned, 3 = fairly concerned, and 4 = very concerned. The total score could range from 16 to 64, with lower scores indicating a low fear of falling.Anthropometric variables, including (i) Weight measured with a Seca^®^ 861 scale, with the participant barefoot and lightly dressed; (ii) Height: measured with a Seca^®^ 222 wall-mounted stadiometer, with the participant barefoot and in an upright position while the sagittal midline of the back touches the vertical bar; and (iii) Body mass index (BMI) calculated using the mean of the two measurements of weight and height as follows: weight (kg)/height^2^ (m^2^).Body composition, including (i) waist circumference reported as the mean of three measurements using a flexible tape measure at the midpoint between the last rib and the iliac crest at the end of a normal exhalation. (ii) Body fat percentage reported as the mean of two measurements using an eight-electrode Tanita^®^ Segmental-418 bioimpedance system (Tanita Corp. Tokyo, Japan). And (iii) Body composition by densitometry (DXA), which allows us to determine fat mass, lean mass, bone density, and bone mineral content.Blood pressure measured using an OMRON^®^ HEM-907 and reported as the mean of two measurements 5 min apart and after a 5-min rest period.Biochemical determinations, including (1) Fasting plasma glucose, apolipoproteins A1 and B, insulin ultrasensitive protein C and endothelial glycocalyx (syndecan-1, syndecan-4 and heparan sulfate proteins) with the Abbott^®^ Cobas 8000 Roche Diagnostics^®^ system; and (2) HbA1c, determined by HPLC (high-performance liquid chromatography) using the ADAMS A1c HA-8180V analyser (Menarini Diagnostics^®^), a method certified by the NGSP (National Glycohemoglobin Standardization Program) and the IFCC (International Federation of Clinical Chemistry and Laboratory Medicine). In addition, BDNF will be measured by enzyme-linked immunosorbent assay (ELISA) (R & D Systems, Minneapolis, MN, USA).Subclinical markers of atherosclerosis and vascular function, including (1) pulse wave velocity (PWv), radial augmentation rate (rAIx), and central augmentation rate (cAIx), which will be measured with the SphygmoCor system (AtCor Medical Pty Ltd. Head Office, West Ryde, Australia); (2) endothelial function: with the ENDO-PAT; and (3) 24-h blood pressure with the MAPA Mobil-O-graph.Adherence to the Mediterranean diet will be measured with the Mediterranean Diet Adherence Screener (MEDAS) questionnaire (27), which includes 12 questions on food consumption frequency and 2 questions on food intake habits considered characteristic of the Spanish Mediterranean diet. Each question will be scored 0 or 1, where the final score could range from 0 to 14.Sleep habits and quality of sleep will be measured with the Pittsburgh Sleep Quality Index (PSQI) (28), which consists of 24 questions, including 19 self-reported and 5 that require secondary feedback from a room or bed partner. Only the self-reported items will be used for the quantitative evaluation of sleep quality, with scores ranging from 0 to 21.Comorbidities measured with the Charlson comorbidity index (29), which consists of the register of 17 comorbidities, with two subcategories for diabetes and liver disease. The total score will be summed from the weighted total mortality risk and disease severity.Level of education: measured as the highest level of education achieved by each participant, classified as: cannot read or write, no education, incomplete primary education, primary education, high school graduation, high school graduation, intermediate university studies, or higher university studies.

**Table 1 tab1:** Study variables.

Type of variable	Specific variables
Primary endpoints	Executive function: inhibition, working memory and cognitive flexibility
	Global cognitive function
Secondary endpoints	Health-related quality of life
	Depression, anxiety, and stress
	Cardiorespiratory fitness
	Muscle strength
Other endpoints	Physical activity: accelerometry
	Physical function
	Concern of falling
	Anthropometry: weight, height, BMI
	Body composition: waist circumference, body fat, body composition
	Blood pressure:
	Blood tests: Fasting plasma glucose, apolipoproteins A1 and B, insulin ultrasensitive protein C, HbA1c, and BDNF
	Markers of atherosclerosis: PWv, rAIx, cAIx, endothelial function, and 24-h blood pressure
	Food consumption
	Sleep habits and quality of sleep
	Comorbidities
Possible confounding factors	Age
	Sex
	Level of education

BMI, body mass index; cAIx, central augmentation rate; HbA1c, hemoglobin glucose; PWv, pulse wave velocity; rAIx, radial augmentation rate.

It should be considered that measurement of accelerometry, body composition with DXA, biochemical determinations, and subclinical markers of atherosclerosis will only be performed in the efficacy and feasibility study.

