### Participants: inclusion and exclusion criteria

Participants will be invited to participate when meeting the following inclusion and exclusion criteria.

Inclusion criteria. Individuals: (1) aged 60–80 years of both genders; (2) retired regardless of the reason for retirement; (3) not meeting frailty criteria according to Fried criteria; (4) are without disabilities for activities of daily living; (5) live independently; (6) without cognitive impairment as determined by the Mini-Mental test greater than 24 (considering the degree of schooling of the participants); and (7) able to walk at least 20 meters with or without walking aids.

Exclusion criteria. Individuals will be excluded when they have any of the following: (1) mobility problems; (2) serious health problems (e.g., recent myocardial infarction, uncontrolled diabetes, or uncontrolled hypertension); (3) orthopedic or neurological disease that prevents training; (4) Alzheimer’s disease or dementia; (5) progressive or terminal illness; (6) acute or chronic illness; (7) history of heart attack; (8) history of vertigo or recent head injury; (9) health problems that may affect the ability to perform physical exercise (e.g., acute and painful joint inflammation, impaired joint function, acute and painful joint inflammation, or deterioration in the ability to perform physical exercise); (10) intake of medications that act at the neuron level (e.g., psychotropic medications); (11) signs of incipient depression; or (12) pathology that impedes the use of the computer application through which the physical exercise program will be developed.

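### Several primary endpoints are each tested at an unadjusted 0.05 while the sample size covers working memory alone, so the stated alpha and power do not hold together for a claim on the primary set

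*Protocol article*

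**What the plan says.** Table 1 (Variables) has two primary rows. One is "Executive function: inhibition, working memory and cognitive flexibility"; the other is global cognitive function. The Variables text gives each component its own instrument: the flanker task for the first (called attention there, inhibition in the table), List Sorting for working memory, the card-sort task for flexibility, and the MMSE for global cognition. It defines no executive-function composite.

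Under Analyses of outcomes, "Mixed regression models will be used in which each outcome variable will be the dependent variable", and then "The results will be considered statistically significant when *p* < 0.05". That section presents itself as a summary of the analysis plan. It gives no adjustment, no testing order and no statement of which primary results make the trial positive.

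Under Sample size, the only effect cited is that a combined programme "can improve working memory in cognitively healthy older adults, with an approximate effect size of 0.9". From this come 21 participants per group at alpha 0.05 and power 0.8, raised to 24 for dropout. These figures are for the efficacy and feasibility phase; the implementation phase is to be sized later from its results.

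**The concern.** The sample size describes one test of one endpoint. The primary objective, as tabulated, is a set of four tests, each read against the same 0.05, and the article does not say how the four combine into a conclusion. As written, a positive efficacy phase could rest on whichever cognitive test crosses the threshold. No planning effect is given for three of the four. The result also carries forward, because the implementation phase takes its sample size from this one, and an endpoint picked out by chance would tend to bring an exaggerated effect into that calculation.

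**Working it through.** **Inputs from the article.** Effect size 0.9, alpha 0.05, power 0.8, 21 per group (Sample size); 1:1 allocation (Recruitment and allocation); four separately measured primary variables (Table 1 and Variables); threshold 0.05 for each outcome (Analyses of outcomes). Sidedness is not stated; two-sided is used because it reproduces the plan's figure.

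**Assumptions, not in the article.** Equal pairwise correlation between endpoints of 0 to 0.8; effects on the three endpoints other than working memory.

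**1. The plan's own figure.** Two-sample t-test, noncentral t, d = 0.9, two-sided 0.05, power 0.8: n = 20.4, rounded up to 21 per group. Power at 21 is 0.812. The figure reproduces. A one-sided test would need only 16.

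**2. Any one of four counts as success, no true effects.** Under independence, 1 − (1 − 0.05)^4 = 1 − 0.8145 = 0.185. The upper bound is 4 × 0.05 = 0.20. For correlated endpoints, by simulation of t-tests with 21 per group:

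| Assumed correlation | Chance of at least one false primary result |
|---|---|
| 0 | 0.185 |
| 0.3 | 0.17 |
| 0.5 | 0.16 |
| 0.7 | 0.13 |
| 0.8 | 0.11 |

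If executive function were a single composite, there would be two tests: 1 − 0.95^2 = 0.0975 under independence, and about 0.08 at a correlation of 0.8.

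**3. All four must be significant.** Alpha is not inflated, but power falls. With d = 0.9 assumed on every endpoint, independence gives 0.812^4 = 0.435. Simulation gives 0.57 at a correlation of 0.5 and 0.67 at 0.8. If one endpoint has a smaller effect, its own power caps the joint power: at 21 per group and alpha 0.05 that is 0.60 for d = 0.7, 0.35 for d = 0.5 and 0.16 for d = 0.3.

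**4. Holm across the four.** The first step uses 0.05/4 = 0.0125. At d = 0.9 and 21 per group, power at that level is 0.62. This is a floor for working memory: if the other three endpoints also have d = 0.9, simulated Holm power for working memory is about 0.70 to 0.73 over the same correlations. Baseline adjustment could add more. If 0.9 is on the unadjusted scale, baseline correlations of 0.3 and 0.5 would raise 0.62 to about 0.67 and 0.77. Power of 0.8 at the 0.0125 step without that gain needs 30 per group, or 30/0.85 = 35.3, rounded up to 36, after 15% dropout.

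**The case against.** **The sample size is not wrong.** The article ties alpha 0.05 and power 0.8 to working memory, and there both hold. This stands. A reader might infer that both figures fail for the trial's primary claim, but no single reading supports that. Under any-of-four, with d = 0.9 throughout, power is 0.92 or more and only alpha fails. Under all-four, only power fails.

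**Four endpoints is one reading.** Table 1 has two primary rows. Four is the likelier count, because each component has its own test and no composite score is defined. Two tests would still give 0.08 to 0.10.

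**The full analysis plan may deal with multiplicity.** It may, and an article need not show all of it. But the point does not rest on silence: the article summarises the plan and states one unadjusted threshold beside a multi-part primary set and a one-endpoint sample size.

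**This is a feasibility phase.** In part. The Design section also gives it the aim of testing efficacy, and it is formally powered. This lowers the severity without removing the point.

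**The MMSE.** Because entry is "without cognitive impairment as determined by the Mini-Mental test greater than 24", a reader might infer that no participant can gain more than 5 of 30 points. The documents do not support this. The same criterion goes on to take schooling into account, and the Variables section puts the impairment cut-off at 20 for those with less than 8 years of education, so some may enter lower and have more room to gain. Nothing here depends on an MMSE ceiling.

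**Conclusion.** The point holds in a limited form. The sample size is sound for working memory alone. For a claim on the primary set, the stated alpha and power do not hold together: either the familywise error is about 0.11 to 0.19 (any of four; 0.08 to 0.10 for two), or power is about 0.435 to 0.67 (all four). The error range depends on assumed correlations of 0 to 0.8. The power range also assumes an effect of 0.9 on every endpoint, which the article does not claim, so it is optimistic. The defect is an unadjusted threshold on several primary endpoints with no success rule, not faulty arithmetic. Should fix.

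**What to change.** For the efficacy phase, choose one of these before any unblinded analysis:

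- **Single primary endpoint.** Name working memory (List Sorting), the endpoint behind the sample size, as primary at two-sided 0.05 and make the other three secondary.
- **Fixed order.** Keep all four primary and test them in a stated order, working memory first, each at 0.05 and only while every earlier test is significant. This suits the stated aims better, since they name global cognition.

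Both keep alpha at 0.05 and the stated power for working memory, with no more participants. The cost is a change to Table 1 and the analysis text and an update to the registration. Three endpoints lose primary or first-tested status.

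If Holm across the four is preferred, restate working-memory power at 21 per group as at least about 0.62, before any gain from baseline adjustment, or enlarge the phase to about 36 per group instead of 24. If executive function is meant as one endpoint, define the composite and apply the same rule to the two.
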